### Adverse events

No serious adverse events are expected as a consequence of the treatment. Slight muscle and joint ache might occur and subjects’ eyes may tire. Health and safety precautions that apply to the XBOX Kinect and the exergame must be strictly observed.

### Data analysis

The data collected (background variables, primary and secondary outcomes) will be tested as to their statistical properties and analysed accordingly. Normally distributed background and control variables will be compared between the groups (experimental vs. control group) using the two-sample *t*-test, and non-normally-distributed variables will be tested using a Wilcoxon rank-sum test. A chi-squared test will be used for the categorical variables. Significant differences might be considered as covariates for further analyses.

The diary entries as well as the execution data obtained from the XBOX and the heart rate during training sessions will be used to provide information about the focus and the frequency of the training as well as about the level of physical exertion during exergaming. These scores will be presented as descriptive summaries. The frequency of exercises (including step count, MET level) during the intervention period will then be compared between the groups and analysed using an independent *t*-test.

In order to test the hypotheses, the primary and secondary outcome variables will be analysed using repeated measures ANOVAs, if applicable. To determine whether a repeated measures ANOVA is applicable, the pre-intervention scores will be tested using an independent *t*-test to determine any differences between groups. Provided no significant differences are found, the repeated measures ANOVAs can be performed. If, on the other hand, significant differences are found, an ANCOVA should be carried out on the baseline data to check the differences. In this case, the pre-intervention scores will serve as covariates, and the post-intervention scores will be introduced as dependent variables.

The significance level will be set at *p* < .05 for all analyses. The results will be reported in accordance with the CONSORT guidelines for clinical trials [80].

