### Outcome measures and time-points of assessment

The study is divided up into five phases (T1-T5). These are discussed in chronological order below (see Fig. 1):Baseline (T1): At the beginning of the study, the participants will be fitted with an accelerometer (Actigraph GT9X), which they are expected to wear during the entire study, to monitor their *physical activity level*. By measuring the acceleration in three-dimensional space, it is for example possible to calculate step counts and MET levels. Participants will be asked to wear the devices at night too, if possible, to obtain data on sleep duration.Pre-intervention measurement (T2): The executive functions, sport motor performance, ADHD symptoms, quality of life and background variables will be measured 7 days after handing over the accelerometer. The measures used to determine the *executive functions:* working memory, cognitive flexibility and inhibition, are based on three standardised tests. They are specifically designed for the age group in question and have proven their age adequacy and sensitivity to changes in executive function performance in previous studies [e.g. 51, 65]: working memory performance will be measured using the colour span backwards [66], in which the number of correct answers will be rated. Cognitive flexibility and inhibition will be measured using the adapted Flanker Test [65, 67, 68], again by computer-assisted means. In this, the scores for accuracy and reaction time will be determined. In addition, an adapted version of the Simon Task [69] will be used. The tests have already been successfully used in several studies [51, 65, 70] and proved to be sensitive enough to detect both acute and chronic effects in children between the ages of 8 and 12 years. The cognitive test battery will last approx. 20 min overall. *Sport motor performance* will be measured using the German Motor Test Battery 6–18, which includes eight test items measuring endurance and coordination [71]. Beyond this, the German version of the Physical Activity Enjoyment Scale will be used to measure the subjective pleasure in physical activity [72]. The Shuttle-run Test [73] will be used to measure physical fitness. The *ADHD symptoms* will be ascertained using the German version [74] of the Conners-3 Scales on Attention and Behaviour [75]. These will be completed by parents and teachers. *Quality of life* will be measured using the Inventory of Quality of Life in Children and Adolescents [76]. This questionnaire will be completed by parents and teachers. The *background variables* will be determined using questionnaires and will include the following: age, sex, height, weight, socioeconomic status [77], exercise behaviour [78], and pubertal development [79], completed by the parents.Intervention phase (T3): The children in the experimental group will train three times a week for approx. 30 min over a period of 8 weeks. The frequency of training and the accuracy will be recorded by the XBOX Kinect and using a Training Diary. In addition, the exercise activity will be recorded by an accelerometer (over a period of 8 weeks) and the heart rate will be recorded by a cardio belt (only during intervention sessions).Post-intervention measurement (T4) and follow-up (T5)*:* At these two times (immediately after the conclusion of the study, and again four weeks later) the tests and questionnaires on the executive functions, quality of life, sport motor performance, attention and behaviour used at T2 will be performed once again.

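### Step count and MET level during the intervention are compared by an unadjusted t-test although the same measures are recorded for a week beforehand; adjusting for that week is a nearly free gain in precision

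*Protocol article*

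**What the plan says.** In the protocol article, under Outcome measures and time-points of assessment, T1 is the baseline phase: "the participants will be fitted with an accelerometer (Actigraph GT9X), which they are expected to wear during the entire study". From the recordings "it is for example possible to calculate step counts and MET levels". The pre-intervention outcomes (T2) "will be measured 7 days after handing over the accelerometer". During the intervention phase "the exercise activity will be recorded by an accelerometer (over a period of 8 weeks"). The design therefore gives each child about one week of recording before the intervention and eight weeks during it, from the same device and in the same units. This agrees with the nine weeks of participation stated under Study design.

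Under Data analysis, the activity comparison concerns "The frequency of exercises (including step count, MET level"), and these values "during the intervention period will then be compared between the groups and analysed using an independent" t-test. No covariate is named.

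Two other sentences in that section mention adjustment:

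- After the group comparison of background and control variables: "Significant differences might be considered as covariates for further analyses".
- For the primary and secondary outcomes, if pre-intervention scores differ significantly: "In this case, the pre-intervention scores will serve as covariates, and the post-intervention scores will be introduced as dependent variables".

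**The concern.** Children differ in how active they habitually are. Some of that difference will carry over from the T1 week into the eight intervention weeks. A two-sample t-test on the intervention-period values treats all of it as noise, so the confidence interval for the group difference is wider than the data require. If one arm happens to contain more active children, that imbalance also passes into the estimate in proportion to the correlation.

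This is the only between-group test that the article names for activity during the intervention. At stake is how much can be learned from it: a wide interval around a null result would say little about whether the arms differed in activity. The test is fixed in the text, so it is not a detail left open for an analysis plan.

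**Working it through.** **Inputs from the article.** Total N = 66, power .80, a small effect, two groups, three measurements and a correlation of .8 between measurements (Participants); α = .05 (Study aims and hypotheses; Data analysis); independent t-test for activity (Data analysis).

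**Assumptions.** Equal allocation, 33 per arm (the ratio is not stated); two-sided test; small effect f = 0.10, the conventional value; r between T1 and intervention-period activity from .3 to .7 (not given).

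**Step 1: the article's own figure.** For the within-between interaction, λ = f²·N·m/(1 − ρ) = 0.01 × 66 × 3 / 0.2 = 9.9, with df 2 and (66 − 2) × 2 = 128. The noncentral F distribution gives power 0.8015, and 66 is the smallest N that reaches .80. The stated sample size reproduces. It was set for the repeated-measures model and not for the activity comparison.

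**Step 2: the planned t-test.** With 33 per arm and 64 df, the difference detectable with 80% power is 0.70 SD. Power for a difference of 0.5 SD is 51.6%.

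**Step 3: adjustment for T1.** ANCOVA leaves a fraction 1 − r² of the variance, so the standard error is multiplied by √(1 − r²), with 63 df. The equivalent sample for an unadjusted test is 66/(1 − r²). For example, at r = .3, 1 − .09 = .91 and 66/.91 = 72.5, which is 10% more. At r = .7, 1 − .49 = .51 and 66/.51 = 129.4, which is 96% more.

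| r | Variance cut | SE multiplied by | Equivalent total N | More children | Detectable at 80% power | Power for 0.5 SD |
|---|---|---|---|---|---|---|
| .3 | 9% | 0.954 | 72.5 | 10% | 0.67 SD | 55.4% |
| .4 | 16% | 0.917 | 78.6 | 19% | 0.64 SD | 58.8% |
| .5 | 25% | 0.866 | 88.0 | 33% | 0.61 SD | 63.7% |
| .6 | 36% | 0.800 | 103.1 | 56% | 0.56 SD | 70.5% |
| .7 | 49% | 0.714 | 129.4 | 96% | 0.50 SD | 80.0% |

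These figures ignore the small cost of estimating the slope, beyond the one degree of freedom, so they slightly overstate the gain.

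**Step 4: chance imbalance.** The difference between the two arms' baseline means has standard deviation √(2/33) = 0.246 SD. It exceeds 0.25 SD in either direction in about 31% of randomisations. A baseline difference of 0.25 SD shifts the unadjusted estimate by 0.25 × r: 0.075 SD at r = .3, 0.125 SD at r = .5 and 0.175 SD at r = .7.

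**Step 5: does another clause already adjust?** The clause on significant differences is permissive, depends on a significance test, and is not tied to the activity comparison. Even if it were applied to T1 activity, a non-significant imbalance would stay in the estimate and the gain in precision would be lost. The ANOVA/ANCOVA rule covers primary and secondary outcomes. Study aims and hypotheses lists these as executive functions, sport motor performance, ADHD symptoms and quality of life. Activity is not among them.

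**The case against.** The strongest defence is that nothing here is an error. Allocation is randomised, so the t-test has the right error rate and is unbiased on average, and its standard error already allows for chance imbalance. That stands. A reader might infer that the comparison is biased or invalid, but the article does not support this. The case for change rests on precision and on how far the one realised estimate may be off.

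Second, the comparison is peripheral. It sits among the training-process data, ahead of the paragraph on testing the hypotheses, and the sample size does not rest on it. That also stands and keeps the point minor. A reader might take this test to be the one that settles whether exergaming adds to a child's activity or displaces other activity. The article gives it no such purpose.

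Third, the gain depends on an unknown r. One week has to predict eight weeks in which one arm's behaviour is deliberately changed, so a low r cannot be excluded, and at .3 the standard error falls by only about 5%. This is correct, and the range starts there for that reason. It would be tempting to say that the baseline week predicts most of the variation, but even r = .7 explains 49%. The planning correlation of .8 belongs to the repeated-measures calculation and should not be carried over to activity.

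Fourth, the plan does allow for covariates. It does so only as an option after a significant difference, which does not secure the gain.

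Finally, children are expected to wear the device, but complete wear is not assured. A complete-case ANCOVA could drop children whom the t-test would keep. That is a real cost, though a small one, and the fix has to deal with it.

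**Conclusion.** The point holds as a nearly free improvement of minor severity. The article names a valid test that does not use a baseline the trial already plans to record. For r between .3 and .7, adjustment cuts the variance by 9% to 49%, equivalent to about 10% to 96% more children in this comparison. It also removes the part of a chance baseline difference that would otherwise carry into the estimate.

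This rests on 33 children per arm, on a T1 week that is largely recorded and not itself altered by allocation, and on the assumed range of r. The seven-day length is inferred from the interval between handing over the device and T2.

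A reader might go on to doubt the primary result or the sample size. Neither is touched: activity is not a primary or secondary outcome, and the figure of 66 reproduces from its stated inputs under the conventional small effect.

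**What to change.** In Data analysis, replace the independent t-test for step count and MET level by a linear model (ANCOVA) for each measure. The intervention-period value is the response, group is the factor, and the child's T1 value of the same measure is a pre-specified covariate. State that the covariate is used whatever any baseline significance test shows, and report the adjusted group difference with its confidence interval.

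Add that children without usable T1 wear time stay in the analysis, for example by simple imputation of the missing baseline value without reference to group.

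The cost is a sentence or two of text and a rule for missing baseline wear. No further visit, device or participant is needed, because the T1 recording is already planned.

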### Study aims and hypotheses

The aim of this study is to evaluate the influence of an exergame intervention, which is characterised by both high physical and high cognitive demands, on the executive functions of children with ADHD. We expect that exergaming will have a positive impact on the executive functions, the sport motor performance, the symptoms of ADHD and on quality of life.

As the primary outcome, we hypothesize that exergaming will positively affect executive function performance compared to controls. More specifically, we expect that the demanding exergame activity that will be carried out over a period of 8 weeks will have a beneficial effect on the key areas—inhibition, working memory and cognitive flexibility—and that we will be able to detect a significant effect (significance level α = .05) with small to moderate effect sizes.

As secondary outcomes, we hypothesize that sport motor performance will be significantly improved by the planned intervention (physically strenuous exergaming). As a further secondary outcome, the influence of the intervention on the symptoms of ADHD will be examined. Based on studies into physical training programmes for children and adolescents with ADHD [42], we hypothesize the intervention to have a positive effect. In addition, quality of life is to be measured as a further secondary outcome serving as an indication of a broad transfer. We expect exergaming to have a positive influence on quality of life. The expectations of registering positive developments with respect to the secondary outcomes are generally somewhat more conservative. Based on the available empirical evidence, we therefore expect to obtain small effect sizes.

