### Participants

In total, 66 children with ADHD between the ages of 8 and 12 years should be examined. Any child that has been diagnosed with the ADHD is eligible to take part in the study. Beyond this, the participants and legal guardians must examine the information relating to the study and give their informed consent to take part in the study. As the well-being of the participants is the main priority, people whose mental or physical integrity might be threatened by the study must not take part in it. For safety reasons, people suffering from a neurological disorder, Tourette syndrome or an epileptic disorder will not be allowed to take part. To recruit the study participants, we will collaborate with elpos Schweiz (an association for parents and caregivers of children and adults with ADHD). The sample size of 66 participants was calculated using G*Power [63] for a general linear model with repeated measures (two comparison groups; three measurements; “within-between interaction”; correlation between measurements = .8), with a power of .80 [64] and a small effect size.

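### A significance test of randomised baseline scores chooses between two non-equivalent hypothesis tests; one prespecified baseline-adjusted analysis should replace it

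*Protocol article*

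**What the plan says.** The Data analysis section applies one rule to all primary and secondary outcomes. First, "the pre-intervention scores will be tested using an independent" t-test between the groups. If it is not significant: "Provided no significant differences are found, the repeated measures ANOVAs can be performed". If it is significant, an ANCOVA replaces the ANOVA: "In this case, the pre-intervention scores will serve as covariates, and the post-intervention scores will be introduced as dependent variables". For background and control variables, the same section compares the groups by significance tests and adds: "Significant differences might be considered as covariates for further analyses".

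The Participants section sizes the trial for only one of the two branches, a "general linear model with repeated measures (two comparison groups; three measurements", tested as a within-between interaction), with "correlation between measurements = .8), with a power of .80 [64] and a small effect size". The Randomisation and blinding section confirms that allocation is random. The time-point section places the repeated tests at T2 (before), T4 (immediately after) and T5 (four weeks later). These are the natural reading of the three measurements.

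**The concern.** Under randomisation any baseline difference is chance, so its significance says nothing about which model is suitable. Equal baseline means are not an assumption of a group-by-time test, and the benefit of ANCOVA does not depend on a significant gap.

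The two branches also answer different questions. The ANOVA was sized as a three-measurement interaction with 2 degrees of freedom. The ANCOVA is a 1-degree-of-freedom comparison of post-intervention scores with no sample-size basis in the article. Each outcome has its own baseline score, so the natural reading is that chance decides, outcome by outcome, which question is tested.

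At stake are the accuracy of the estimate in a trial that happens to be imbalanced, and power that the collected baseline scores could supply.

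**Working it through.** **Inputs from the article.** N = 66, two groups, three measurements, rho = .8, power .80, a small effect (Participants); alpha = .05 (Study aims and hypotheses; Data analysis).

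**Assumptions.** Small means Cohen's f = 0.10; 1:1 allocation (33 per arm); two-sided tests; no dropout; equal correlations between visits; the same effect at T4 and T5. The article gives no support for rho = .8, so rho = .5 is shown as the lower end of an assumed range.

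**1. The plan's own figure.** For the interaction, lambda = f² x N x m / (1-rho) = 0.01 x 66 x 3 / 0.2 = 9.9, with df 2 and 64 x 2 = 128. The noncentral F gives power .8015, and N = 65 gives .795, so 66 is reproduced. Two measurements would need 82, so the trial was sized on the three-measurement test.

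**2. The effect in SD.** With group differences of 0, d and d at the three visits, f = d/√18, so d = 0.10 x √18 = 0.424 SD.

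**3. What the pre-test lets through.** It is significant when the gap exceeds t(.975, 64) x √(4/66) = 1.998 x 0.2462 = 0.49 SD. That happens in 5% of cases per outcome; the other 95% go to the ANOVA.

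**4. Error given a gap g.** The expected post-intervention difference is d + rho x g. The interaction subtracts all of g, leaving d - (1-rho) x g.
- At the threshold, rho = .8: 0.2 x 0.49 = 0.10 SD (23% of 0.424).
- At the threshold, rho = .5: 0.5 x 0.49 = 0.25 SD (58% of 0.424).
- These are ceilings. The mean absolute gap among non-significant trials is about 0.18 SD, so the typical error is about 0.035 SD (rho = .8) or 0.09 SD (rho = .5).

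**5. Type I error (simulation, 33 per arm).**
- All trials, two-stage rule: about .048 at rho = .8 and .044 at rho = .5.
- Trials with a non-significant gap above 0.35 SD (about 10% of trials): about 7% at rho = .8 and 8-10% at rho = .5, against about 5% for ANCOVA.

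**6. Power for 0.424 SD.** The ANCOVA standard error is about √(v x 4/66), with v = 1-rho² for T4 alone and v = (1+rho)/2 - rho² for the T4/T5 mean. So v is .36 and .26 at rho = .8, and .75 and .50 at rho = .5.

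| Analysis | rho = .8 | rho = .5 |
|---|---|---|
| Planned rule with three-measurement ANOVA | .80 | .40 |
| ANCOVA, T4 only | .80 | .49 |
| ANCOVA, mean of T4 and T5 | .91 | .66 |

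**The case against.** The strongest defence is that the rule does little harm on the plan's own terms. Much of that stands, and it rules out several stronger readings that a reader might infer.

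- **That estimates stay uncorrected unless the pre-test is significant.** They do not. The interaction removes the full baseline gap, so it over-corrects. An uncorrected post-score comparison would be off by rho x g, about 0.39 SD at the threshold with rho = .8, against 0.10 SD here.
- **That false positives are inflated.** Over all trials the rule is unbiased and slightly conservative. The excess exists only conditional on an imbalance.
- **That ANCOVA always has more power.** At rho = .8 the planned three-measurement rule equals T4-only ANCOVA (.80 each). A like-for-like loss at T4 (.77 against .80) arises only if the ANOVA is cut to two visits, which is not what the trial was sized on. The gain at rho = .8 comes from adjusting for baseline and testing both later visits together on one degree of freedom.
- **That a known share of outcomes will switch model.** Any such figure needs a count of scores and their correlations, and the article gives neither.
- **That covariates must be chosen by significance.** The text only permits it.

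The article may also condense a fuller plan. But this rule is stated outright, not left open, so an unseen document does not remove it.

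What the defence does not supply is a purpose for the pre-test. It identifies nothing but chance, and it withholds regression adjustment from the moderate imbalances where adjustment would help.

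**Conclusion.** The point holds as a should-fix. A chance result selects between two tests that are not equivalent, only one of which the trial was sized for. Given an imbalance that the pre-test misses, the change estimate is off by at most about 0.10 SD at the stated correlation, and by up to 0.25 SD if the correlation were .5. Averaged over all trials there is neither bias nor type I inflation. Against an analysis that adjusts for T2 and uses both later visits, the planned rule gives up about 11 points of power at rho = .8 (.91 - .80) and 26 at rho = .5 (.66 - .40).

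The bias and type I figures rest on 1:1 allocation, full follow-up and equal correlations. The power figures also need f = 0.10 and a constant effect at T4 and T5; an effect that fades by T5 would shrink the gain from using both visits. The rho = .5 results are a sensitivity range, not a figure from the article.

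**What to change.** In the Data analysis section, delete the t-test of pre-intervention scores as a gate, and delete the option to take significant baseline differences as covariates. For every primary and secondary outcome, prespecify one analysis to be used whatever the baseline shows:

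- ANCOVA of the T4/T5 mean on group and the T2 score, or a longitudinal model of T4 and T5 adjusted for T2; or
- ANCOVA of T4 on group and the T2 score, if T4 is the target time point. This is also the choice if the waiting-list group starts the exergame before T5, on which the article's text is silent.

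Report baseline characteristics descriptively, without tests.

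The cost is one degree of freedom per model and some rewording; the T2 scores are already collected. Because the tested effect changes, the sample-size statement in Participants should be restated for the chosen model. Under the assumptions above, 66 children give about .80 (T4 only) or .91 (T4/T5 mean) at rho = .8, and about .49 or .66 at rho = .5.

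### Every analysis is set at p < .05 on a primary outcome of three domains and several scores with no success rule: if any one score suffices, the error could reach up to about 14% (3 scores) or 26% (6 scores) were they independent

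*Protocol article*

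**What the plan says.** All of this is in the protocol article.

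- **Primary hypothesis** (Study aims and hypotheses): "As the primary outcome, we hypothesize that exergaming will positively affect executive function performance compared to controls". The section then names three key areas, "inhibition, working memory and cognitive flexibility", and expects a significant effect at α = .05.
- **Measurement** (Outcome measures and time-points of assessment): the executive-function measures "are based on three standardised tests". Colour span backwards covers working memory, "in which the number of correct answers will be rated". For the other two domains, "Cognitive flexibility and inhibition will be measured using the adapted Flanker Test", and for that test "the scores for accuracy and reaction time will be determined". An adapted Simon Task is added, with neither its domain nor its scores stated.
- **Analysis** (Data analysis): the primary and secondary outcome variables go into repeated measures ANOVAs, or an ANCOVA if the groups differ at baseline. The error level is fixed by "The significance level will be set at *p* < .05 for all analyses".
- **Sample size** (Participants): 66 children, from G*Power, for a within-between interaction with two groups, three measurements, correlation .8, power .80 and a small effect.

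**The concern.** The sample size and the α of .05 belong to one test, whereas the primary outcome offers several. The article does not say whether one significant score is enough to confirm the primary hypothesis, whether each domain is a separate claim, or whether all three must succeed. These rules have different error rates and different power.

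If one score is enough, .05 is not the error rate of the primary conclusion. If all three domains must succeed, .80 is generally not its power. Flanker accuracy and reaction time can also move in opposite directions, and nothing says which of them decides. A reader of the eventual result could not tell what standard of evidence the primary claim had met.

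**Working it through.** **1. Reproduce the plan's sample size.** Inputs from Participants: k = 2 groups, m = 3 measurements, ρ = .8, power .80. The small effect has no number, so f = .10 is assumed. α = .05 comes from Data analysis. For the G*Power within-between interaction (sphericity assumed):

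- λ = f²·N·m/(1 − ρ) = .01 × 66 × 3/.2 = 9.9
- df₁ = (k − 1)(m − 1) = 2; df₂ = (N − k)(m − 1) = 64 × 2 = 128
- Power from the noncentral F at α = .05: .8015. N = 64 gives .788.

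So 66 is the smallest even total that reaches .80. This supports f = .10 and shows that the calculation covers one test at .05.

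**2. Count the scores.** Three if there is one per domain. Five if colour span gives 1 and the two Flanker scores are each used for two domains (1 + 2 × 2). Six with one Simon score added. The counts of five and six are assumptions, because the article does not list the scores to be analysed.

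**3. Rule A: any one significant score suffices.** With no effect and independent scores, the chance of at least one p < .05 is 1 − .95^k. Counting only results that favour exergaming, it is 1 − .975^k.

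| Scores | Either direction | Favouring exergaming |
|---|---|---|
| 1 | 5.0% | 2.5% |
| 3 | 14.3% | 7.3% |
| 5 | 22.6% | 11.9% |
| 6 | 26.5% | 14.1% |

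For normal test statistics with a common correlation of .5, the either-direction figures are about 12.5% (3), 18% (5) and 21% (6). A simulation of the group-by-time F test itself (33 per arm assumed, 20,000 trials per scenario) agrees:

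| Correlation between scores | 3 scores | 6 scores |
|---|---|---|
| .3 | 13.3% | 24.3% |
| .5 | 12.8% | 20.9% |
| .7 | 11.5% | 16.7% |
| .9 | 8.5% | 11.4% |

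Every case exceeds 5%. In the same runs, counting only significant results whose pre-to-post change favoured exergaming roughly halved the rates.

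**4. Rule B: all three domains must succeed.** The error stays below 5% (at most about 2% in the simulations). With .80 power per score, however, joint power is .8³ = .512 if the scores are independent. It rises towards .80 only as their correlation approaches 1.

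**5. Power with Holm on three domain scores, N = 66.** Using λ = 9.9 and df 2 and 128:

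| Holm step | α | Power |
|---|---|---|
| First (strictest) | .05/3 = .0167 | .66 |
| Second | .05/2 = .025 | .71 |
| Last | .05 | .80 |

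Keeping .80 per score at .05/3 would take N = 86.

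The preliminary baseline test that chooses between ANOVA and ANCOVA was not modelled.

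**The case against.** **The size is not established.** A reader might infer that the protocol carries a 14% to 26% chance of falsely claiming that exergaming improves executive function, instead of 5%. The documents do not support that as a flat statement. It needs independent scores, although two Flanker scores from one test in the same child are unlikely to be independent. It needs a count of scores that the article does not give. It also counts significant harm: for a claim of improvement the independent-score range is about 7% to 14%, and the single-test comparator is 2.5%. This objection stands, and the figures are ceilings for a given count.

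**The any-score rule is not in the text.** The hypothesis names all three areas and can be read as requiring all of them, or as three separate claims. This also stands, and it makes the problem an unstated rule and not a fixed error rate. It does not rescue the plan, because the all-domains reading moves the shortfall from α to power.

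**An article leaves detail to the full protocol or analysis plan.** Which Flanker or Simon index serves which domain may well be settled there. So a reader should not infer that scores will be chosen after the results are known; the article does not show that. But it is not silent on α. It fixes .05 for every analysis, and a later adjustment would contradict that sentence.

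**The trial is early-stage.** The Discussion concedes limited prior evidence and foresees further comparisons if results are favourable. That tempers the consequences, but it does not define the primary claim.

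**Conclusion.** The point holds in limited form. The protocol sets .05 for all analyses of a multi-domain, multi-score primary outcome, sizes the trial for one test, and states no primary score, success rule or multiplicity control.

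- If any one score suffices, the either-direction error is up to about 14% (3 scores) or 26% (6 scores) under independence, and about 12.5% or 21% at correlation .5. It is roughly half that for results favouring exergaming, against 2.5% for one test.
- If all three domains must succeed, the error is controlled, but power for the primary conclusion is about .51 under independence and generally below .80.

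The direction of the problem under each rule does not depend on the assumed counts. The exact size does, and it depends on the correlation between scores as well. The power figures rest on f = .10, which reproduces the planned 66.

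**What to change.** Amend the outcome and analysis sections as follows.

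1. Name one primary score per domain: number correct on colour span backwards for working memory, one named score for inhibition, and one named score for cognitive flexibility.
2. Test the three with Holm at overall .05, and replace the blanket .05 sentence accordingly.
3. Make the remaining Flanker and Simon scores secondary, and state that they are not multiplicity-controlled.
4. Restate power per domain score at N = 66, with f = .10 declared: about .66 at the strictest step, .71 at .025 and .80 at .05.

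A single primary score, a composite, or an explicit all-domains rule with its power restated would also resolve the point.

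The cost is a short text amendment and a less favourable stated power. No more children are needed if that power is accepted. Keeping .80 at the strictest step would need 86 instead of 66.
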